### Blinding

In the experimental groups, participants will not be informed of the group assignment, the type of diagnosis, or the treatment that they will receive. Data managers and the statistician will also be blinded. Only the trial administrator (a steering committee of the Department of Good Clinical Practice, Wuxi People’s Hospital), who will be responsible for assigning the participants into different subgroups and monitoring the entire trial process, will be not blinded. Moreover, the clinical research physicians will be blinded to the assignment of group 1, whose treatment will be decided based on their clinical practice, while they will have access to the diagnostic and treatment allocation data for group 2. The clinical physicians will be responsible for learning how to use the blinding method to communicate with the participants to ensure diagnosis and treatment blinding. The blinding procedure will be conducted until the data are locked and the trial is completed. Unblinding will only be permitted in case of a medical emergency or when a participant quits the trial. All cases of unblinding will be documented.

### Interventions

#### Healthy control group

As mentioned above, participants will only be recruited in the healthy control group if they do not have PCOS, metabolic conditions, or any other disorders that may influence sex-related hormones and they are not using any drugs that could also influence sex hormones. A medical evaluation will be conducted to confirm eligibility, after which the trial team will collect information regarding the patient’s medical history, conduct a physical examination, and collect blood samples from eligible participants for further investigation.

#### Clinical index group

For the clinical index group, blood samples and medical information of all eligible participants will be collected. Based on several guidelines and clinical experience, subgroup 1 (participants with hormone metabolism disorders) will receive orally administered Diane-35 once a day for 21 days, after which the treatment will be paused for 7 days. Subgroup 2 (participants with lipid metabolism disorders) will receive orally administered metformin (2000–2500 mg) once a day based on their clinical condition. The entire treatment period will be at least 6 months. During the trial, blood samples will be collected three times (week 0, week 15 ± 1, and week 26 ± 1) for metabolomic evaluation to assess changes. However, the detection information will be blinded to all participants and clinical research physicians to avoid influencing the results. All clinical research physicians will be required to have majored in endocrinology and metabolism or gynecological endocrinology for at least 10 years. They must also be employed as an attending physician for > 5 years. Finally, they must receive professional training on clinical trials and pass a test to ensure consistent performance in the study methods.

#### Metabolomic index group

Most of the interventions for the metabolomic index group will be similar to those for the clinical index group. The main difference is that the division of the subgroups will be based on metabolomic indices. The physicians in this group will be informed of the allocation of participants to the subgroups and will provide the corresponding treatment scheme to all participants. The physicians will not be allowed to change the scheme during the trial and will remain blinded to the metabolomic results to minimize the possibility of any influence on treatment decisions.

### Concurrent treatment of patients

All other treatments for PCOS will be banned during the trial, including oral contraceptives, broad-spectrum lipid drugs, and any other drugs that might influence the results. However, participants may receive any treatment not related to PCOS and will be instructed to use condoms during sexual intercourse. Any change in concurrent treatment will be recorded at every visit.

### Outcome measurements

The healthy control group will remain enrolled in the trial until all their samples are collected. For the experimental groups, the primary outcome will be the changes in their relative PCOS condition evaluated using clinical indices. The main clinical index that will be evaluated is the LH/FSH ratio.

Secondary outcomes will be assessed using other indices, signs, and symptoms, as described in the 2018 Chinese Endocrine Society clinical practice consensus on PCOS [1] such as sex hormone-related indices (FSH, LH, prolactin, estradiol, progesterone, testosterone, anti-Müllerian hormone (AMH), and vitamin D), blood lipid-related indicators (total cholesterol, triglycerides, HDL, LDL, Apo A1, Apo B, lipoprotein(a), free fatty acids, and high-sensitivity C-reactive protein), and endocrine-related indicators (glucose and insulin (at 0, 30, and 120 min) and blood uric acid). To help evaluate the outcomes, three metabolic markers will also be used, namely, palmitoyl sphingomyelin, cyclic guanosine monophosphate, and DHEAS. Ultrasound results will also be evaluated, and the number and diameter of follicles in both ovaries will be measured.

Safety outcomes will include any severe impairment in liver function or inability of the patient to tolerate symptoms (e.g., nausea and vomiting caused by metformin) related to the therapeutic drugs. Such outcomes will be monitored after each treatment session (1 month) using the hepatic function test. An exploratory outcome will be complete recovery from PCOS after treatment within 26 weeks.

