PCOS has diverse phenotypes [15–17] and thus requires individualized treatment. The European Society of Endocrinology [2] proposed four phenotypes, including a type without hyperandrogenemia. When diagnosing the disease, it was suggested that abnormalities in steroidogenic enzymes, prolactin excess, and thyroid problems need to be ruled out. In China, the classification of subtypes and treatment of PCOS are mainly based on clinical indices, such as sex hormones (e.g., follicle-stimulating hormone (FSH), luteinizing hormone (LH), LH/FSH ratio, free testosterone, dehydroepiandrosterone (DHEAS), androstenedione, sex-hormone-binding globulin), serum lipids (e.g., total cholesterol, triglycerides, low-density lipoprotein cholesterol (LDL-C), high-density lipoprotein cholesterol (HDL-C), apolipoprotein (Apo) A, Apo B), and the results of oral glucose tolerance tests and immunoreactive trypsinogen tests [1]. This heterogeneity in diagnostic criteria could significantly lead to misdiagnoses. Therefore, it is urgent to explore a new detection method to standardize the classification of phenotypes and establish an efficient diagnostic and treatment strategy for PCOS. The development and application of new technologies, such as genomics, proteomics, and metabolomics, provide a new direction for diagnosing PCOS phenotypes. However, in genomics, although the findings of genome-wide association studies have implications, the direct pathogenic gene for PCOS has not been found yet. In proteomics, some scholars have identified potential biomarkers for PCOS phenotyping, but their clinical application is limited because proteins, or amino acids, are highly susceptible to interference, which can bias the results. Lastly, due to the high sensitivity and specificity of metabolomic methods, it can be assumed that some metabolic markers can be used to distinguish whether patients with PCOS have high androgen levels.

In the attempt to classify PCOS phenotypes, recent studies have adopted various measurements such as nuclear magnetic resonance [18], liquid chromatography/mass spectrometry [19], and others [20, 21]. In our previous study [3], using ultra-high-performance liquid chromatography/quadrupole time-of-flight mass spectrometry, we found two subgroups of patients with PCOS: one with hormone metabolism disorders and the other with lipid metabolism disorders.

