## Methods

### Study design

This is a prospective, multicenter, analyst-blinded, randomized controlled trial. Subjects will be grouped into one healthy control group and two parallel experiment arms, as follows: (1) people without PCOS (healthy control group), (2) patients diagnosed with PCOS based on clinical indices (experimental group 1), and (3) patients diagnosed with PCOS based on metabolomic indices (experimental group 2). A total of 276 participants, including 60 people without PCOS and 216 patients with PCOS, will be recruited. The 216 patients with PCOS will be randomly assigned to the two experimental (diagnosis) groups in a 1:1 ratio. After group assignment, medical detection results, relative information, and biological samples will be collected from all three groups. Additionally, the blood samples from all participants will be tested using metabolomic methods for further study, while the analysis results will be totally blinded to all participants and their research physicians. Based on our previous study [3], we will categorize patients with PCOS into two subgroups: patients with hormone metabolism disorders (subgroup 1) and patients with lipid metabolism disorders (subgroup 2).

The two diagnosis groups will be automatically divided into the two different subgroups according to patient characteristics. The main difference is that in group 1, diagnosis will be based on clinical indices [1], such as clinical signs and symptoms and ultrasonography findings, while in group 2, diagnosis will be based on metabolomic indicators. All patients will receive treatment according to their subtype group, and the treatment will consist of Diane-35 or metformin. The intervention period for all experimental groups will be 6 months, and the results will be evaluated after the completion of three constant treatment sessions (3 months).

Outcomes will be assessed, and the data will be analyzed by someone blinded to the assignment of participants. The study design is shown in Fig. 1, and the timeline is presented in Figs. 2 and 3.

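### A pooled LH/FSH difference between the arms compares two label-and-treat strategies; it does not by itself show that metabolomic subtyping is more accurate

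*Protocol article*

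**What the plan says.** All references are to the Protocol article.

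- **Endpoint.** Under Outcome measurements, "the primary outcome will be the changes in their relative PCOS condition evaluated using clinical indices", and then "The main clinical index that will be evaluated is the LH/FSH ratio". No other index is named for the primary outcome. The next paragraph begins "Secondary outcomes will be assessed using other indices, signs, and symptoms" and lists the hormone, lipid, glucose/insulin and ultrasound measures. The Fig. 3 caption also treats LH/FSH as the main index.
- **Label and drug.** Study design: "All patients will receive treatment according to their subtype group, and the treatment will consist of Diane-35 or metformin". Clinical index group: "subgroup 1 (participants with hormone metabolism disorders) will receive orally administered Diane-35", while the lipid subgroup receives metformin. The Metabolomic index group section keeps the interventions largely the same and changes the basis of the subgroup division.
- **Who sets the label.** In group 1, treatment follows the physicians' clinical practice (Blinding). In group 2 it follows metabolomic indices, and physicians may not change the scheme.
- **Analysis.** Statistical analyses compares quantitative indices between whole groups by analysis of variance. Nothing stated there balances or standardises the drug mix between arms.
- **Aim.** The abstract's Discussion and the end of the Background ask whether metabolomic indices are more accurate and more effective than clinical characteristics for diagnosing phenotypes.
- **Data at hand.** Study design: "the blood samples from all participants will be tested using metabolomic methods for further study". The Clinical index group section places the first of these samples at week 0.

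**The concern.** The label and the drug are one-to-one, so changing the labelling rule can change two things at once: how many patients get the drug that suits their subtype, and how many patients get each drug. Only the first concerns diagnostic accuracy. The second moves the arm mean whenever the two drugs act differently on the outcome.

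Randomisation does not remove the second component, because the drug mix is set after randomisation by the rule under test. The outcome also belongs to one side of the subtype division: the Background lists LH/FSH among "sex hormones (e.g., follicle-stimulating hormone (FSH), luteinizing hormone (LH), LH/FSH ratio", separately from the lipid indices. At stake is the sentence the trial wants to write at the end. A significant LH/FSH difference, in either direction, could be credited to better diagnosis when it reflects a different drug mix.

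**Working it through.** **Inputs from the document.** 108 patients per arm, 20% dropout, two-sided 0.05 (Sample size calculation; Statistical analyses). Evaluable per arm: 108 × 0.8 = 86.4, taken as 86. The document gives no LH/FSH difference or SD, so it has no figure of its own to reproduce on this point.

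**Assumptions, not in the document.** D is the difference between the drugs in mean LH/FSH change, in SD units. p1 and p2 are the shares on one given drug in arms 1 and 2. m is the gain from receiving the drug that matches the subtype.

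**Pooled contrast with no matching benefit (m = 0).**

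Arm difference = (p2 − p1) × D

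SE² = [1 + p1(1 − p1)D²]/86 + [1 + p2(1 − p2)D²]/86

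Example, p1 = 0.5, p2 = 0.7, D = 1: difference 0.20; SE = √(1.25/86 + 1.21/86) = 0.169; two-sided rejection at 1.96 is 0.219.

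| Shares | D = 0.5 | D = 1 |
|---|---|---|
| 50% vs 60% | 0.062 | 0.090 |
| 50% vs 70% | 0.098 | 0.219 |
| 40% vs 70% | 0.160 | 0.428 |

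With D = 0, or equal shares, the figure is 0.05.

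**Can the pooled result point the wrong way?** Take the document's 90.9% and 87.5% as the metabolomic method's sensitivity and specificity for subtype 1. Assume 50% true subtype 1, a clinical rule of 95% and 40%, D = 1 in favour of subtype 1's drug, and m = 0.25.

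- Shares on subtype 1's drug: metabolomic 0.5 × 0.909 + 0.5 × 0.125 = 0.517; clinical 0.5 × 0.95 + 0.5 × 0.60 = 0.775.
- Proportion correctly labelled: 0.892 against 0.675.
- Arm difference, metabolomic minus clinical: (0.517 − 0.775) × 1 + 0.25 × (0.892 − 0.675) = −0.258 + 0.054 = −0.204 SD.

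In simulation the less accurate arm wins significantly about 22% of the time and the more accurate arm about 0.05%. This shows that a reversal is possible, not that it is expected.

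**Within week-0 metabolomic subtype.** Treat the metabolomic subtype as the true one. Arm 2 then gives every patient the matching drug. Suppose arm 1 gives the other drug to 20% of each stratum:

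- Stratum 1: 0.2 × (D + m)
- Stratum 2: 0.2 × (m − D)

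A pure drug effect therefore takes opposite signs in the two strata. Dividing each difference by 0.2 gives D + m and m − D, and their equal-weight average is m: the drug main effect cancels.

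**Precision.** With 43 per arm per stratum (equal strata assumed), D = 1 and m = 0.25, the stratum differences are +0.25 (SE 0.229) and −0.15 (SE 0.220). The SE of the averaged estimate is ½ × √[(0.229/0.2)² + (0.220/0.2)²] ≈ 0.79 SD, against a true value of 0.25. Power is about 6%.

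**The case against.** The strongest reply is that drug choice is how a diagnostic strategy acts. If shares and drug effects differ, the strategies really do differ on LH/FSH, and rejecting the null is correct. That stands. A reader might take 6% to 43% as inflated type I error; it is not. The figures are the chance of detecting a true strategy difference that contains no matching benefit. Only its attribution to accuracy is open.

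Other stronger readings also lack support:

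- **That an arm can win by giving more Diane-35.** No section states either drug's effect on LH/FSH, in size or direction. The exclusion criterion that sets Diane-35 beside hormonal products names metformin in the same list.
- **That LH/FSH is the sole measure.** The text calls it the main index among clinical indices. The Discussion also plans a comparison of sensitivity and specificity, and Data collection and monitoring records an assessment of diagnostic accuracy. These do not repair the pooled contrast, but accuracy is not to be judged on LH/FSH alone.
- **That the clinical arm chooses its drug on the outcome variable.** The Background's statement that "the classification of subtypes and treatment of PCOS are mainly based on clinical indices, such as sex hormones" describes practice in China. For group 1, Study design gives signs, symptoms and ultrasonography as examples. Choosing treatment on a baseline value does not bias a randomised comparison, and the Discussion says LH/FSH correlates with the metabolomic results too.

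It may also be said that drug shares and stratified results belong in an analysis plan that is not shown. That is fair for the reporting detail. The endpoint, the label-to-drug link and the intended conclusion are fixed in this document.

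**Conclusion.** The point holds as a limit on what may be concluded. The pooled comparison validly answers which label-and-treat strategy gives the better LH/FSH change. It does not by itself answer which method subtypes more accurately, because it adds (difference in drug share) × (drug difference on LH/FSH) to any matching benefit.

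The first component could be nil or substantial. At a 10-point share gap the chance of a significant result is 6% to 9% for D of 0.5 to 1 SD; at 30 points it is 16% to 43%. It stays at 5% if the drugs act equally or the shares match. Everything beyond the label-to-drug structure rests on assumed D, m and shares. This is a cheap improvement that changes the permitted conclusion, not a defect that invalidates the randomised comparison.

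**What to change.** Analysis and wording only; no new samples and no change to treatment.

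1. State that the pooled LH/FSH difference supports a claim about the strategy's effect on LH/FSH, not about diagnostic accuracy.
2. Report the share of patients on each drug, by arm.
3. Report the randomised LH/FSH contrast within each week-0 metabolomic subtype, and read beside it one prespecified lipid or insulin index from the panel already drawn.
4. If a matching effect is to be estimated, divide each stratum's arm difference by the share of arm 1 in that stratum given the other drug, then average the two strata with equal weight. Label the result supportive.

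Do not require arm 2 to be no worse in both strata. By the stratum 2 formula, a truly better method is expected to fail that rule whenever D exceeds m. At D = 1 and m = 0.25 both point estimates are non-negative only about 21% of the time; with no benefit at all (D = 0.5, m = 0) the rule still passes about 22% of the time.

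Cost: some analysis work and a narrower headline. Stratum results are less precise than the whole-arm result, the estimate in item 4 has little power, and it becomes very unstable if few arm 1 patients in a stratum receive the other drug.

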### Safety evaluation

AEs will be evaluated at every visit and will include any unexpected or unfavorable response that occurs during or after treatment. Although these events may not have a causal relationship with the variables in this study, the investigators will need to ensure that all AEs are reported and recorded in the subject’s medical records. In this trial, AEs are defined as disorders that (1) hinder one’s ability to work or are life-threatening (especially liver dysfunction) or (2) lead to hospitalization or prolong department or hospital stay. Remedial treatment should be given immediately to resolve any observed AE, and all AEs will be reported to the responsible units, ethical committees, and trial administrator to decide whether the participant ought to remain in or drop out of the trial. Regardless of the decision, all participants with an AE will be followed up until the event has been resolved or the condition has become chronic or stable.

The study should not cause any additional harm to the participants. In case of serious unexpected harm to a participant related to the study, we will shoulder the relevant expenses (including the diagnosis and treatment) and follow up the condition of the participant until recovery.

### Follow-up

To evaluate the accuracy and efficacy of diagnosis, safety, and the superior effects of individual interventions, a follow-up via telephone (or via face-to-face interviews, emails, text messages, or WeChat) will be conducted 6 months after the trial. During the follow-up, no participants will undergo special therapy except for routine cervical care. At weeks 30, 34, 38, and 41, the outcome assessor will call the participants to investigate their PCOS condition, asking mainly about menstrual cycle length and frequency, the appearance of hyperandrogenism (e.g., weight loss, acne, excessive facial and body hair), and pregnancy. Participants are welcome to inform the assessors of their clinical symptoms and AEs via face-to-face meetings, emails, telephone calls, text messages, or WeChat at relevant time points.

### Blinding and credibility tests

Metabolomic evaluation with blinding will be completed at weeks 0, 15, and 26. The implementation of the blinding strategy will be crucial for the trial. The credibility rating for both the diagnostic methods and different types of treatment will be estimated using a credibility test at weeks 15, 26, and 41 during the follow-up period.

### Data collection and monitoring

Data on basic patient characteristics will be collected and recorded by screeners when participants are recruited. Clinical signs and symptoms, physical examination findings, metabolomic evaluation results, short- and long-term outcomes, assessment of diagnosis accuracy and treatment efficiency, and details of the AEs will be recorded by trial assessors and clinical researchers in case report forms (CRFs).

Completed CRFs will be checked and reviewed by a five-person steering committee, which is composed of two supervisors of the major trial center, a data statistician, and two data administrators. The committees are completely independent from the research team and will be constantly blinded to the group allocation.

All data entry and management procedures will be conducted in an OpenClinica System (version 3.12) database. The committee members will need to be qualified in data analysis and will have been trained uniformly.

To ensure the accuracy of data, two data administrators will independently perform data entry and validation. Any issues with the information in the CRFs will be reported by the data administrators to the steering committee. Any revisions will be modified by the administrators according to feedback from the committee. Once the accuracy of data is confirmed, the electronic database will be locked while real-time tracking and monitoring will remain open.

The steering committee and the Department of Good Clinical Practice in Wuxi People’s Hospital will monitor the entire trial (e.g., checking the progress of recruitment, participant data including CRFs, the protocols for researchers, informed consent forms, and any other study-specific files) and audit the trial conduct at least once a month.

All information will be made available to the investigators whose proposed use of the data has been approved by the relevant committee for up to 15 years following publication. The findings will be presented at conferences and published in peer-reviewed journals. A summary of the findings will be provided to the participants upon request via telephone.

### Sample collection and handling

The actual dates and times of sample collection will be recorded in the laboratory requisition form. Instructions for the collection, handling, and storage of samples are found in the laboratory manual that will be provided.

The standard procedure for plasma separation will be performed as follows:
Fresh anticoagulated peripheral blood will be collected in the EDTA anticoagulant tubeThe fresh peripheral blood will be centrifuged at 1700 G at 4 °C for 10 min, and the upper plasma will be carefully collected to avoid touching the lower layers of red blood cells and white blood cellsThe collected plasma will be centrifuged at 2000 G at 4 °C for 10 min, and the supernatant will be decantedThe plasma will be divided and placed in separate containers and frozen at − 80 °C in a refrigerator for later use

